### Purpose

The aim of this pilot trial is to investigate the preliminary effect and feasibility of a 12-week multimodal intervention consisting of physiotherapy (functional, balance, and strength training), protein-rich nutritional supplementation, and anabolic steroid (INT) compared with physiotherapy (functional, balance, and strength training), protein-rich nutritional supplement, and placebo (CON) in rehabilitation following hip fracture surgery on fractured limb knee-extension muscle strength at 14-week follow-up.

We hypothesize the following:
An intervention consisting of physiotherapy, nutritional supplementation, and anabolic steroid is a feasible and preliminary safe treatment in elderly patients with hip fracture when initiated in the acute orthopedic ward and continued for 12 weeks.This multimodal intervention (physiotherapy, nutritional supplementation, and anabolic steroid) is more efficacious in improving muscle strength and physical function 14 weeks after hip fracture surgery than physiotherapy, nutritional supplementation, and placebo.

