#### Safety parameters

The following values are assessed: hemoglobin, hematocrit, creatinine, carbamide, sodium (Na^+^), potassium (K^+^), calcium, international normalized ratio (INR), liver tests, PSA, and glucose.

For the following parameters, safety thresholds are defined: hematocrit (safety threshold, values > 0.50), liver tests (albumin, alanine aminotransferase, γ-glutamyltransferase, bilirubin) (safety threshold, liver test values > 3 times the upper limit of normal), and PSA (safety threshold, increase to > 50%).

Other safety parameters are blood pressure (assessed using a digital blood pressure monitor, measured in mmHg) and facial hirsutism (assessed using the two face-related items of the modified Ferriman-Galwey hirsutism score, 0–8 points) [56], hoarseness (assessed through weekly interviews and hospital controls every 3 weeks), edema (assessed through weekly interviews and hospital controls every 3 weeks), and falls (a question regarding falls will be part of an interview guide used for the weekly telephone calls). Other AEs/adverse reactions (ARs) will be assessed through weekly interviews and hospital controls every 3 weeks.

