#### Feasibility outcomes

Feasibility will be assed according to the following aspects: number of eligible patients, inclusion rate per month, feasibility and suitability of outcome measures, acceptability of the treatments to the patients, adherence to the treatment, retention to the scheduled controls and follow-up, and number and severity of AEs.

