### Data monitoring

The trial will be conducted in accordance with the International Council for Harmonisation of Technical Requirements for Pharmaceuticals for Human Use (ICH) principles of good clinical practice (GCP). The project is registered with EudraCT (identifier 2017-001543-13) and is monitored by the independent GCP unit at Copenhagen University Hospital Bispebjerg. The GCP unit will monitor the project throughout the trial and assure that the trial is executed, registered, and reported according to the protocol, written standard operating procedures, GCP, and Danish legislation. Scheduled monitoring visits will be conducted throughout the trial. The first initiating visit is prior to commencement of the trial. The focus of the following visit is on monitoring the trial master file, protocol compliance, data quality, and informed consent. Further, selected trial data are monitored (e.g., inclusion, dropout, completion, primary outcome, trial medication, randomization, allocation, drug compliance, medicine accounting, AEs). No additional auditing is planned.

AEs and ARs related to the trial will be recorded in the CRF throughout the trial period, starting from the day of the first injection and ending at week 16. The relationship (causality) between the AE and the trial medication and severity will be assessed by the principal investigator or any one of the medical doctors trained in the protocol. The summary of product characteristics for Deca-Durabolin is used as a reference when assessing if a serious AR is unexpected or expected.

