It should be noted that the following conditions are considered to occur often after hip fracture surgery and can lead to prolonged hospitalization: nausea, vomiting, dizziness, postoperative urine retention due to catheterization, pain or irritation in relation to the bladder due to catheterization, diarrhea, pneumonia and cardiopulmonary influence, hemoglobin (Hb) < 9.7 g/dl and consequently blood transfusion, and divergent blood tests due to surgery. These will not be registered as AEs during hospital admission. Expected pain from the operation site will not be registered as an AE during the trial period. Further, edema of the fractured limb is common in the postoperative period, and especially for patients with trochanteric fractures compared with those with cervical femoral fractures [4], and will not be reported as an AE. Laboratory test results beyond the reference interval will be recorded as an AE only if they cause a clinical action.

All AEs/ARs will be followed until stabilization by either the relevant hospital department or the patient’s general practitioner.

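### Listed in-hospital conditions, including pneumonia, cardiopulmonary events and transfusion for low hemoglobin, are kept out of the AE data even when they arise after the first injection, so the AE outcome is undercounted for that period

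*Protocol article*

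**What the plan says.** All references are to the Protocol article.

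- **AE window.** Data monitoring has AEs and adverse reactions recorded "starting from the day of the first injection and ending at week 16".
- **Start of treatment.** Trial medication places the first injection at baseline. Outcome places the baseline assessment on postoperative days 3 to 10.
- **Exemption.** Data monitoring then lists conditions regarded as frequent after this surgery and able to prolong the stay. They include "pneumonia and cardiopulmonary influence, hemoglobin (Hb) < 9.7 g/dl and consequently blood transfusion", and also "postoperative urine retention due to catheterization", catheter-related bladder symptoms, nausea, vomiting, dizziness, diarrhea and deviating blood tests caused by surgery. Of these it says "These will not be registered as AEs during hospital admission".
- **Edema.** The same section says that edema of the fractured limb is common "and will not be reported as an AE", with no end date. Safety parameters nevertheless names "edema (assessed through weekly interviews and hospital controls every 3 weeks" among the items followed.
- **Use of the data.** Purpose hypothesises a "feasible and preliminary safe treatment in elderly patients with hip fracture when initiated in the acute orthopedic ward". Feasibility outcomes includes "number and severity of AEs". Statistical analyses treats safety and feasibility descriptively.

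**The concern.** The exemption rests on how often the conditions occur. In a blinded, placebo-controlled trial that is a reason to register them. When an event is common in the background, judging single cases cannot separate drug from surgery, but a count by randomised arm can.

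Two of the exempted items matter most. Pneumonia and cardiopulmonary influence carry no qualifier of cause. Low hemoglobin with transfusion is an event on which the drug could act, since Trial medication says that nandrolone stimulates red cell formation.

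The AE count and the safety hypothesis are meant to inform a larger trial. If these events are absent from the count for the acute period, the pilot passes on an incomplete AE profile for the setting named in its own hypothesis.

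**Working it through.** The plan states no figure on this point, so the main check sets the rules side by side.

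**1. Does the exemption overlap the AE window?** Recording opens at the first injection, which is tied to baseline on postoperative days 3 to 10. General trial treatment procedures separates this step from what follows discharge, and Purpose speaks of starting on the acute ward. For any patient still admitted after the injection, the AE window is open while the exemption applies. The two rules overlap from injection to discharge.

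**2. Is the exemption limited within that overlap?** It is not limited by seriousness or severity, nor by onset before or after the injection. Some items are limited by cause: urine retention and bladder symptoms to catheterization, deviating blood tests to surgery. Pneumonia and cardiopulmonary influence have no such limit.

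**3. Is the rule consistent within its own section?** Data monitoring says that a laboratory value outside the reference interval counts as an AE only if it leads to clinical action. Transfusion is a clinical action, so low hemoglobin with transfusion would meet that test. The list removes it during admission.

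**4. What decides registration?** Discharge does. The same pneumonia on the same postoperative day is an AE in a patient at home and not in one still on the ward. The section itself says that these conditions can prolong the stay, so a complicated patient may remain under the exemption longer. Registration thus depends on something that happens after randomisation.

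**5. What is still captured?**
- In-hospital AEs that are not on the list.
- Listed conditions after discharge, up to week 16.
- Deaths and readmissions, which are separate secondary outcomes. Readmissions do not recover events during the index stay.
- Laboratory safety parameters and blood pressure at baseline and weeks 3, 6, 9, 12 and 14.

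**6. Edema.** As a safety parameter, edema is asked about weekly and checked at three-weekly controls, with no exclusion of the fractured limb. The weekly calls begin after discharge. Fractured-limb edema is therefore described after discharge, but it never enters the AE count. Between injection and discharge the article names no assessment of it beyond baseline.

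**7. Size.** The article gives no event rate. It gives no length of stay either, and Protocol amendment says only that the stay is short for some patients. With the planned 48 patients and an assumed share p having an exempted event between injection and discharge, the expected number is 48 × p:
- p = 5%: 48 × 0.05 = 2.4 patients
- p = 10%: 48 × 0.10 = 4.8 patients
- p = 20%: 48 × 0.20 = 9.6 patients

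These values show scale only and are not estimates.

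**8. A figure that does not measure the loss.** With 24 patients in the active arm and no events, the one-sided 95% upper bound is 1 − 0.05^(1/24) = 11.7%. This reflects the size of the arm under complete recording. For an exempted event a zero count comes from the rule itself, so no bound can be given.

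**The case against.** A reader might infer that the safety question cannot be answered at all for the admission. The documents do not support that. The list is closed, other in-hospital AEs and deaths are captured, and laboratory safety data are collected whatever the AE status. What is lost is a set of event types for part of the stay.

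A reader might also infer that edema goes unobserved, or that all urinary retention is exempt. Neither is so. Edema is collected and described after discharge as a safety parameter, and retention is exempt only when attributed to catheterization.

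Three further objections have weight:

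- **Low information.** Restoring the events would seldom reveal an excess in 48 patients. If 7 patients had events, split 5 against 2 with 24 per arm, two-sided Fisher p is about 0.42. This stands as a limit on inference. But the plan makes no test of safety. It describes, and a description needs the events.
- **No tilt between arms.** The rule is stated in advance and applies to both arms under blinding. Nothing in the documents shows that it favours an arm. The complaint is undercounting and a missing comparison.
- **Text not shown.** The article does not set out its rules for serious AEs, and the full protocol may keep a serious listed event. This is a real uncertainty. As printed, however, the exemption has no such exception.

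Approval by the ethics committee and the medicines agency shows that the rule was accepted. It does not make the AE count complete.

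**Conclusion.** The concern holds in a limited form. The exemption in Data monitoring cuts into the AE window opened in the same section. The number and severity of AEs are undercounted, and the exempted event types, above all pneumonia, cardiopulmonary influence and low hemoglobin with transfusion, cannot be compared between arms from the first injection to discharge. That period belongs to the setting named in the safety hypothesis. Fractured-limb edema is a smaller inconsistency: it is missing from the AE count throughout and has no stated assessment between injection and discharge.

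The size is unknown. The range of about 2 to 10 patients of 48 rests wholly on an assumed 5–20% incidence. A short stay after the injection would make it smaller. The conclusion also assumes that the full protocol has no separate rule that retains serious listed events. This is a change worth making while inclusion is still open. It does not invalidate the trial's other safety data.

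**What to change.** Reconcile the exemption in Data monitoring with the AE window in the same section and with edema under Safety parameters:

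- From the first injection, record in the CRF each listed condition that begins or worsens after it, with date, severity and seriousness, whether or not the patient is still admitted.
- Tabulate these events descriptively by arm, together with edema of the fractured limb, including the interval from injection to discharge.
- Keep the list of expected conditions for reporting purposes only.
- For patients already enrolled, extract the events from the medical records of the index stay, by staff blinded to allocation. Readmissions are already taken from this source.

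The cost is a checklist in the CRF, slightly more data entry per admission, the retrospective extraction, and higher AE counts in both arms. The higher counts should be explained in the report. Patients whose events were extracted afterwards should be identified, since severity and onset may be less complete for them. No treatment or stopping rule changes.

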### Statistical analyses

Descriptive statistics will be used for presenting baseline characteristics. Continuous data will be examined for normality of distribution using Q-Q plots. Data will be presented as mean (SD) when normally distributed, otherwise as medians (q1–q3) or as frequencies with percentages.

The statistical analysis of the primary outcome will be two-sample *t* test or Wilcoxon rank-sum test as appropriate to determine systematical differences in change scores between the intervention and control groups. For the secondary outcomes, tests will be performed using either chi-square or Fisher’s exact test for categorical data or two-sample *t* test or Wilcoxon rank-sum test for continuous data. Analysis of safety parameters and feasibility endpoints will be descriptive. The level of significance will be set at *P* < 0.05, and confidence intervals (CIs) will be displayed at 95% CI around differences.

The analysis will follow the intention-to-treat principle and include all randomized patients. To create a full analysis set, missing data will be imputed using a multiple imputation technique. Secondary analysis will be conducted for both primary and secondary outcomes on the per-protocol data, where patients are excluded if they are not compliant with the trial. Compliance in relation to per-protocol analysis is defined as 75% intake of nutritional supplement, 75% completed training sessions, and 100% received injections. No interim analyses will be conducted.

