**Fig. 2 Fig2:**
[figure not shown]
Schedule for enrollment, intervention, and outcome assessments (SPIRIT)

The baseline assessment might extend over 2 days in order to avoid patient exhaustion, and it will be conducted during the time period from postoperative day 3 until postoperative day 10. The follow-up assessment is conducted during week 14 from time of randomization (± 7 days from time of randomization). The control every 3 weeks is conducted within 3, 6, 9, and 12 weeks (± 7 days from time of randomization).

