#### Primary outcome

Change in maximal isometric knee-extension strength (N∙m/kg) in the fractured limb (maximal voluntary torque per kilogram body mass) from baseline to the 14-week follow-up. Knee-extensor strength is chosen as the primary outcome because it is closely related to the exposure (strength training), which is what we want in this pilot trial. Hence, we consider the outcome a surrogate outcome measure for a more clinically meaningful one, such as mobility. Pertaining to this, knee-extensor strength is associated with impaired mobility [4, 33].Knee-extensor strength is measured using a belt-fixed handheld dynamometer (Commander Muscle Tester; JTECH Medical, Midvale, UT, USA) [3, 27, 28]. The test is conducted as described by Kronborg et al. [3] with the patient seated on the bedside, with hips and knee joint angle in 90-degree flexion and hands placed on the mattress for support. The lever arm length is measured by tape measure between the lateral epicondyle of the femur and the center of the dynamometer transducer pad placed 4 cm above the lateral malleolus of the tibial bone. Four trials must be completed, and the highest obtained value in Newtons (N) will be used for analysis. Tests are performed with standardized verbal encouragement. The isometric knee-extension strength is expressed in N∙m/kg, which is derived from the units of force measured in Newtons (N) multiplied by the corresponding lever arm measured in meters (m), divided by the weight of the patient in kilograms (kg).

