### Sample size

The sample size is determined on the basis of the primary outcome (change in knee-extension strength of the fractured limb) and calculated to detect a between-group difference in the change score of 0.2 N∙m/kg in favor of the intervention group using Lehr’s formula with an SD of 0.22 N∙m/kg. The difference in change scores of 0.2 N∙m/kg is defined by the authors, and it is a larger difference than what could be considered the minimal clinically important difference. Because we only wish to explore the potential of effect in this pilot trial [57], and not establish effect, we argue that it is acceptable. The SD of 0.22 N∙m/kg is obtained from a previous study [3]. Hence, we acknowledge that if this trial shows feasibility and preliminary effect of the intervention, confirmatory effect will need to be demonstrated in at least one phase III-like confirmatory trial. On the basis of this estimate, 20 patients are needed in each group using a standard of 80% power and type I error rate of 5%. Forty-eight patients are therefore planned for inclusion in the present trial to allow for an expected dropout rate of 20%. In case of dropout, new patients will be enrolled in the trial to ensure a minimum of 20 patients in each group who have completed the intervention.

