### Randomization and allocation

The patients will be randomly assigned to one of the two groups by a 1:1 allocation ratio. Block randomization (blocks of 2 and 4) will be used, and patients will be stratified for type of fracture (cervical femoral versus trochanteric hip fracture) and sex. The allocation sequence is computer-generated (random number generator) by a qualified person not involved in the trial. The allocation sequence is retained in a locked cabinet by the person generating the sequence. To ensure allocation sequence concealment, sequentially numbered, opaque, sealed envelopes are used. When a person is included in the trial, the coded envelope is broken by the nurse injecting the trial medication. The envelopes contain information on allocation and a registration form used for medicine accounting. The envelopes will be retained by the nurse injecting the medication and kept in the nurse’s office, which is geographically separated from the hip fracture unit and the Department of Physiotherapy.

Information about allocation will not be revealed before all data analysis has been performed.

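### The primary test on change scores adjusts for neither baseline strength nor the stratification factors: it is valid, but may be less precise than the data allow

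*Protocol article*

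**What the plan says.** All references are to the protocol article.

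- **Primary outcome** defines the endpoint as "Change in maximal isometric knee-extension strength (N∙m/kg) in the fractured limb" from baseline to 14 weeks, so baseline strength belongs to the endpoint itself.
- **Statistical analyses** compares the arms by a two-sample t test or "Wilcoxon rank-sum test as appropriate to determine systematical differences in change scores between the intervention and control groups". No covariate, stratified test or adjusted sensitivity analysis is named; the only secondary analysis is per protocol. All randomised patients are to be analysed, and "missing data will be imputed using a multiple imputation technique".
- **Randomization and allocation** uses blocks of 2 and 4, and "patients will be stratified for type of fracture (cervical femoral versus trochanteric hip fracture) and sex".
- **Outcome** (text below Fig. 2) has the baseline assessment "conducted during the time period from postoperative day 3 until postoperative day 10".
- **Sample size** aims to "detect a between-group difference in the change score of 0.2 N∙m/kg in favor of the intervention group". It adds that "The SD of 0.22 N∙m/kg is obtained from a previous study" and arrives at 20 per group and 48 in total.
- **Discussion** says that the estimates will be used to size a confirmatory trial, and that going on to that trial will not rest on statistical significance.

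**The concern.** The design balances the arms on sex and fracture type, but the analysis leaves both out. If either factor predicts change in strength, the unadjusted standard error includes between-stratum variation that the design has already removed from the comparison. The interval is then too wide and the test conservative.

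For baseline strength, a change score assumes that each unit of baseline carries over fully to week 14. Baseline is taken a few days after surgery, when strength has just dropped, so a slope of exactly 1 is doubtful. With any other slope, chance imbalance in baseline leaves noise in the difference that a covariate would remove.

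Precision is at stake. The trial is small, its recruitment is reported as lower than expected, and its estimate and interval are to inform a larger trial.

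**Working it through.** **Inputs from the document (Sample size).** Difference 0.2 N∙m/kg, SD 0.22 N∙m/kg, 80% power, 5% type I error, 20 per group. The text does not say whether 0.22 is the SD of change or of a single measurement. It is taken first as the SD of change, which is how the calculation uses it.

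**Assumed inputs, not in the document.** The correlation r between baseline and week-14 strength, the ratio k of week-14 SD to baseline SD, and the share R² of change-score variance explained by the strata.

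**Step 1: the plan's own figure.** Lehr's formula gives 16 × (0.22/0.2)² = 19.36, rounded up to 20 per group. Noncentral-t power at 20 per arm is 80.0%. The total is 40 × 1.2 = 48. The stated figures reproduce for the stated test.

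**Step 2: adjusting for baseline.** With baseline SD σ and week-14 SD kσ:

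- Var(change) = σ²(1 + k² − 2rk)
- Var(week 14 given baseline) = k²σ²(1 − r²)
- Ratio = k²(1 − r²)/(1 + k² − 2rk), which is (1 + r)/2 when k = 1

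The effective SD is 0.22 × √ratio. Power is noncentral-t at 20 per arm, with three further degrees of freedom spent on baseline, sex and fracture type. No gain from the strata is credited here.

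| k | r = 0.3 | r = 0.5 | r = 0.7 | r = 0.8 |
|---|---|---|---|---|
| 1.0: ratio | 0.65 | 0.75 | 0.85 | 0.90 |
| 1.0: power | 93% | 90% | 86% | 84% |
| 1.2: ratio | 0.76 | 0.87 | 0.97 | 1.00 |
| 1.2: power | 89% | 85% | 81% | 80% |
| 1.3: ratio | 0.81 | 0.91 | 0.99 | 1.00 |
| 1.3: power | 88% | 83% | 80% | 80% |

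The gain vanishes when the regression slope rk is near 1, for example 0.8 × 1.2 = 0.96.

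For k = 1, the 95% CI half-width falls from 0.141 to 0.122 at r = 0.5 and to 0.134 at r = 0.8. The planned test would need about 20/0.75 = 27 and 20/0.90 = 22 patients per arm to match.

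**Step 3: leaving out the strata.** If balanced strata explain a share R² of change-score variance, the true size of the nominal 5% test is about 2[1 − Φ(1.96/√(1 − R²))]:

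- R² = 5%: 1.96/√0.95 = 2.01, size 4.4%
- R² = 10%: 1.96/√0.90 = 2.07, size 3.9%
- R² = 20%: 1.96/√0.80 = 2.19, size 2.8%

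A simulation of stratified blocks of 2 and 4 with 40 patients (5,000 runs per setting) agrees:

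| R² | Unadjusted size | Unadjusted power | Stratum-adjusted power |
|---|---|---|---|
| 0% | 5.3% | 80% | 79% |
| 10% | 4.0% | 81% | 83% |
| 20% | 2.9% | 83% | 88% |

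When the strata explain nothing, adjusting for them costs under one point of power. The gains in steps 2 and 3 should not be added, because strata and baseline may explain the same variance.

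**Step 4: the other reading of 0.22.** If it is the SD at one time point, with k = 1, the SD of change is 0.22 × √(2(1 − r)), which equals 0.22 only at r = 0.5. Change-score power is then about 66% at r = 0.3 and 95% at r = 0.7. With baseline adjustment it is about 84% and 98%.

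**The case against.** The best case for the plan is that nothing in it is invalid. Baseline precedes randomisation and both arms share the same assessment window, so the unadjusted difference is unbiased. Omitting the strata makes the test conservative, not liberal. The planned test also matches the sample-size calculation, which reproduces. All of this stands.

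The size of the gain is also open to challenge. The ratio (1 + r)/2 needs equal SDs, and if spread widens as patients recover, the gain can disappear, as the rows for k = 1.2 and 1.3 show. The share of variance explained by the strata is assumed as well. Differences between sexes or fracture types in the level of strength may largely cancel in a change per kilogram of body mass. This too stands, and it is why the result is a range that includes nil.

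The figure of 20 per arm is the planned minimum of completers. The analysis set is all randomised patients, 48 as planned, with imputation.

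A reader might infer more in two respects:

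- **That the plan ignores baseline.** It does not; the change score subtracts it. What is missing is an estimated slope.
- **That the choice between t and Wilcoxon, or pooling a rank test over imputations, is a flaw in itself.** The choice is tied to Q-Q plots, and finer rules commonly sit in an analysis plan that is not shown. A rank-based shift estimate with a bootstrap standard error could be pooled. These are secondary details.

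The objection does not reach the remaining point. The protocol states its primary test outright, and an adjusted model improves that stated rule at almost no cost. That the decision to continue will not rest on significance lowers the importance of power, but not that of a precise estimate and interval.

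**Conclusion.** The point holds as a matter of efficiency. The unadjusted test on change scores is valid and unbiased, but it can give away precision that baseline strength and the stratification factors would supply.

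At 20 per arm, difference 0.2 and SD of change 0.22, baseline adjustment gains between nothing and about 13 points of power (80% to at most 93%). This assumes r of 0.3–0.8 and a week-14 to baseline SD ratio of 1.0–1.3. If the strata explain an assumed 5–20% of change-score variance, the nominal 5% test has a true size of about 4.4–2.8%. The direction is secure; the size is not, because the document gives none of the three assumed quantities.

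The document does not support a reading that the planned result would be biased, that the type I error would be inflated, or that the sample size is wrong for the stated test. For a pilot this is a worthwhile improvement, not a fatal flaw.

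**What to change.** Make the primary analysis one pre-specified linear model of week-14 knee-extension strength on arm, baseline strength, sex and fracture type. Modelling change with the same covariates gives the same arm effect. Fit it in each imputed data set, pool by Rubin's rules, and report the adjusted mean difference with its 95% CI. Keep the t or Wilcoxon test on change as a sensitivity analysis.

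Apply the same model only to continuous secondary outcomes that have a baseline measurement. Activity monitoring is described only from the 12-week control, so adjust it for the stratification factors alone. For quality of life, vitality and depression, the baseline refers to the time before the fracture, and the report should say so where that value is the covariate.

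The cost is a change of wording and three degrees of freedom. The plan already collects every covariate.
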